## Abstract

**Background:**

Clinical rehabilitation for brachial plexus injury is difficult in terms of chronic pain and dysfunction. Physiotherapy is considered a routine intervention for rehabilitation. Common physical therapy may require a variety of instruments. One approach that does not need instruments, but belongs to the field of complementary and alternative medicine, is naprapathy. Naprapathy, also called Tuina in China, has been applied in rehabilitation after brachial plexus injury for a long time. Naprapathy can relieve chronic neuropathic pain, promote local blood circulation, and improve body edema. Naprapathy can passively help improve motor functions in patients with peripheral nerve injury. However, the efficacy of naprapathy in improving rehabilitation after brachial plexus injury is unclear.

**Objective:**

This study aims to evaluate the additional value of naprapathy when combined with conventional physical therapy for the treatment of brachial plexus injury.

**Methods:**

This will be a single-center randomized controlled trial. A total of 116 eligible patients with brachial plexus injury will be randomly divided into an experimental group (naprapathy plus physical therapy group) or a control group (physical therapy group). The participants will be followed up for 4 weeks of treatment. Observation outcomes will include the visual analog scale score, upper limb index, electromyography findings, and adverse reactions, among others. The measuring points for outcomes will be the baseline and the completion of treatment. In addition, a quality control group independent from the research team will be set up to control the quality of the trial. Finally, the data will be analyzed using SPSS software (version 21.0; IBM Corp).

**Results:**

The study is recruiting participants. The first participant was enrolled in September 2021. As of January 2023, a total of 100 participants have been enrolled. The trial is expected to be completed by September 2023. The study protocol was approved by the Ethics Review Committee of Yue Yang Hospital affiliated with the Shanghai University of Traditional Chinese Medicine (2021-012).

**Conclusions:**

One limitation of this trial is that we will be unable to achieve strict double-blinding because of the features of naprapathy. The trial aims to contribute reliable evidence for decision-making in naprapathy for treating brachial plexus injury.

**Trial Registration:**

Chinese Clinical Trial Registry ChiCTR2100043515; http://www.chictr.org.cn/showproj.aspx?proj=122154

**International Registered Report Identifier (IRRID):**

DERR1-10.2196/46054

## Introduction

Brachial plexus injury (BPI) is one of the most challenging problems in modern medicine because of its high disability rate, surgical difficulty, and complex sequelae [1]. It is mostly caused by injuries such as a motorcycle accident, birth injury, bruising, puncture injury, fracture, dislocation, and lung apex tumor resection [2-5]. Sensory impairment or muscle paralysis and atrophy, which cause partial or complete upper limb motor and sensory dysfunction, may place a great burden on the patient's life and mental health [6,7]. With the development of microsurgical technology in recent decades [8], great progress has been made in the treatment of BPI, especially in terms of surgical treatments [9,10], allowing good conditions for the functional recovery of patients' limbs to be provided. There are also some rehabilitation methods, such as medium-frequency electrical stimulation, infrared irradiation, ultrasound therapy, and so forth, but the effects are not satisfactory [11,12].

The ability of an injured nerve to regenerate is closely related to the repair time, with 1 to 3 months after injury being considered the “golden period” for nerve repair [13]. However, with a delayed diagnosis, the prognosis is poor. Surgical repair is only performed in preparation for the treatment of BPI; rehabilitation is the beginning of treatment and is necessary after surgery [14]. Due to differences in the condition of patients with BPI, physical therapy should be used to relieve pain, eliminate swelling, prevent scar adhesion, and joint contracture; promote nerve regeneration; and prevent muscle atrophy and joint stiffness [15,16].

At present, physical rehabilitation therapies commonly used after BPI, such as neuromyoelectric stimulation, intermediate frequency electrotherapy, and hand function training [17-19], have certain effects on upper limb function, but the effect of rehabilitation on hand function remains limited.

Naprapathy (also called Tuina therapy in traditional Chinese medicine) [20] consists of physical stimuli acting on the human body through manipulation to cause physiological responses in tissue fibers. Through the regulation of nerve reflexes and body fluids, therapeutic effects on damaged areas can be achieved. Naprapathy can promote capillary dilation, increase blood circulation, and improve muscle blood circulation such that the condition of damaged tissue can be improved and the tissue will be repaired [21]. Swelling and cramping can also be reduced or alleviated. Our previous study showed that naprapathy can improve the pain threshold in rats with neuropathic pain caused by BPI, increase the expression of β-endorphin and gamma-aminobutyric acid in the reward circuit in the brain [22], and relieve chronic neuropathic pain in rats. These findings may represent one of the neurological mechanisms of naprapathy. Naprapathy not only exerts an analgesic effect but also provides a certain comfort for patients. Patients with BPI are also willing to undergo naprapathy in the clinic. However, there is a lack of clinical research on naprapathy in the treatment of BPI. Therefore, we designed this randomized controlled trial (RCT) to evaluate the additional effects of naprapathy when combined with conventional physical therapy on pain and hand motor function in patients with BPI.

## Methods

### Study Design

This clinical trial will be an open-label RCT designed to compare naprapathy plus physical therapy and physical therapy in treating BPI. This protocol has been registered on the Chinese Clinical Trial Registry (2100043515) and will be performed in accordance with the Declaration of Helsinki. The study flowchart is shown in Figure 1.

**Figure 1 figure1:**
[figure not shown]
Study flowchart. BPI: brachial plexus injury.

### Ethics Approval

The study protocol was approved by the ethics review committee of Yue Yang Hospital affiliated with the Shanghai University of Traditional Chinese Medicine (2021-012). Any changes including eligibility criteria, outcomes, and so forth should be reported to the Ethics Review Committee. The ethics committee of Yueyang Hospital affiliated with the Shanghai University of Traditional Chinese Medicine will audit the whole procedure during the clinical trial conducted independently from investigators and the funder. The participants signed the informed consent and agreed to the primary and secondary analyses of their data without additional consent. All the study data are deidentified. This trial has also been registered in the Chinese Clinical Trial Registry (2100043515). The results of the preliminary study will be published in a professional journal.

### Patient and Public Involvement

Patients and the public are involved in the design of the study. They reviewed the study proposal and attended the design meetings. Patients and the public will be included in all research communications.

The inclusion criteria are as follows: (1) aged 18 to 70 years; (2) BPI diagnosed by history, physical examination, electromyography, or surgical exploration more than 2 weeks after nerve surgery; (3) agreement to provide written informed consent.

The exclusion criteria are as follows: (1) concurrent damage to major organs, such as the heart, kidneys, liver, and so forth; (2) severe cardiovascular or cerebrovascular disease, liver or kidney dysfunction, metabolic disease, or mental illness; (3) chronic illness, physical discomfort, frailty, severe neurosis, or pregnancy; (4) primary brachial plexus pain or brachial plexus neuritis; (5) brachial plexus pain due to cervical spondylosis, tennis elbow, carpal tunnel syndrome, frozen shoulder, biceps tenosynovitis, thoracic outlet syndrome, or other secondary causes.

The participants will be withdrawn if they have the following: (1) missing or incomplete patient treatment records, which would affect the final data analysis; (2) treatment with other methods at the same time; (3) any severe adverse reactions or other emergent symptoms during the treatment (such as aggravation of disease or severe depression and the need for special treatment).

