### Randomization

In this clinical trial, a total of 116 participants with BPI will be randomly assigned to either group A (naprapathy plus physical therapy) or group B (physical therapy) at a 1:1 ratio. The random sequence will be generated using SAS software (version 9.3; SAS Institute, Inc). The coauthors randomizing the participants are not linked to any statistical work.

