### Outcomes

#### Primary Outcome Indicator

The primary outcome measure will be the change in visual analog scale score relative to baseline at 4 weeks.

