### Time Points of Outcome Measurement

Outcomes will be evaluated at 2 time points: baseline and at the completion of treatment. An overview of the outcomes measured at the different time points is shown in Table 1.

**Table 1 table1:** Case data collection timetable.

Time point	Baseline	Posttreatment
Written informed consent	✓	
Concomitant treatment	✓	
Disease history	✓	
History of medication	✓	
Brunnstrom functional assessment	✓	✓
VAS^a^	✓	✓
EMG^b^ examination	✓	✓
Participant self-evaluation		✓
Adverse events		✓
Safety analysis		✓

^a^VAS: visual analog scale.

^b^EMG: electromyography.

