### Sample Size

Our previous study indicated that 58.5% of patients with BPI showed improvements in upper extremity function and muscle strength [23]. In this clinical trial, the rate of upper extremity function recovery is expected to be 75% in the naprapathy group and 55% in the physical therapy group. With α=.05 and β=.01, a total of 52 participants will be needed, as calculated using SPSS software (version 21.0; IBM Corp). According to the previous study, a 10% withdrawal rate will also be considered; therefore, each group will include at least 58 participants.

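### Withdrawing randomized participants for incomplete records, other treatment or worsening can cost them their 4-week VAS and can bias the open-label primary comparison

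*Protocol article*

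**What the plan says.** In the Protocol article, the section Patient and Public Involvement lists inclusion and exclusion criteria and then a separate set of withdrawal criteria. The first two are "missing or incomplete patient treatment records, which would affect the final data analysis; (2) treatment with other methods at the same time". The third is "any severe adverse reactions or other emergent symptoms during the treatment (such as aggravation of disease or severe depression and the need for special treatment". All three concern events that arise once treatment is under way, after allocation.

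Other sections that bear on this:

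- Study Design: "This clinical trial will be an open-label RCT designed to compare naprapathy plus physical therapy and physical therapy in treating BPI".
- Randomization: 116 participants are "randomly assigned to either group A (naprapathy plus physical therapy) or group B (physical therapy) at a 1:1 ratio".
- Primary Outcome Indicator: "The primary outcome measure will be the change in visual analog scale score relative to baseline at 4 weeks".
- Time Points of Outcome Measurement: "Outcomes will be evaluated at 2 time points: baseline and at the completion of treatment".
- Sample Size: "a 10% withdrawal rate will also be considered", which leads to at least 58 per group.
- Naprapathy: after any adverse event treatment is suspended, and the investigator decides whether it ends.

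The article does not say that a withdrawn participant is still assessed at 4 weeks or analysed in the assigned arm.

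**The concern.** Randomization protects the comparison only if the people compared are those who were randomized. Each withdrawal reason can break that link.

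- **Worsening** is itself a poor outcome. A rule that takes such people out of the study tends to make their arm look better than it is.
- **Other treatment** plausibly follows poor response. In an open-label trial, participants without the add-on know they lack it.
- **Severe reactions** can differ by arm. Assessment of Safety and Adverse Events lists events that naprapathy may cause, among them local pain, which bears directly on the VAS.
- **Incomplete records** give no reason to end someone's participation. The criterion is justified by its effect on the analysis, so it works as a rule for removing data.

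At stake is the validity of the primary VAS comparison. If withdrawal differs between the arms, in rate or in its link to outcome, the estimate mixes the effect of naprapathy with the effect of who was left to be measured.

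**Working it through.** **1. Does withdrawal mean loss of the primary outcome?** Set the sections side by side. The first criterion is tied to the final analysis. The Sample Size section counts withdrawals as lost numbers. There is one post-baseline assessment, at completion of treatment. On this text, a participant withdrawn before completion has no 4-week VAS.

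**2. The plan's own figure.** Inflating 52 for 10% withdrawal: 52 / (1 − 0.10) = 57.8, rounded up to 58. This reproduces the 58 per group. The article calls 52 a total, but 58 per group follows only if 52 is read as per group, and that reading is used below. Whether 52 follows from the stated recovery rates is a separate matter, and nothing here depends on it.

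**3. Assumed extreme.** Inputs: the article's 10% withdrawal rate; 52 per arm remaining; and three assumptions of this review: no true effect, a normal outcome with SD 1, and the worst 10% lost in one arm while the other arm loses 10% at random.

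- Shift of the affected arm: φ(1.2816) / 0.9 = 0.1755 / 0.9 = 0.195 SD, in that arm's favour.
- Standard error of the difference: √(2/52) = 0.196 SD.
- Standardized shift: 0.195 / 0.196 = 0.994.
- Two-sided type I error: P(Z > 1.96 − 0.994) + P(Z < −1.96 − 0.994) = 0.167 + 0.002 = 0.169, about 17%.

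This holds the SD at 1 in both arms. Removing one tail also shrinks the SD, and a simulation of the same case (58 randomized per arm, 52 kept, Welch t test) gives about 20%.

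**4. How far this depends on the assumptions.** Simulation with no true effect, 58 randomized per arm, Welch t test at two-sided 0.05 and 10,000 replicates. Except in the equal-loss row, the bias favours the arm that loses more.

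| Withdrawn, one arm vs other | Link of withdrawal to outcome | Bias (SD) | Type I error |
|---|---|---|---|
| 10% vs 0% | complete (worst removed) | 0.20 | 21% |
| 10% vs 5% | complete | 0.09 | 11% |
| 15% vs 5% | complete | 0.17 | 20% |
| 10% vs 10% | complete | 0.00 | 8% |
| 10% vs 0% | moderate (correlation 0.5) | 0.10 | 8% |
| 10% vs 5% | moderate | 0.04 | 6% |
| 15% vs 5% | moderate | 0.09 | 8% |

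Equal removal of the worst 10% leaves no mean bias when there is no effect. The 8% in that row arises because trimming makes the estimated SD too small. The article gives only one overall withdrawal rate, so no row can be singled out as the expected one.

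**The case against.** The strongest reply is that loss from the analysis is inferred. The article says participants are withdrawn; it does not say that their data are dropped. A 10% allowance is ordinary in trials analysed by intention to treat, and analysis populations may be defined in a plan not shown. This stands in part: the absence of a named analysis set is no finding, and the allowance alone proves nothing. But an analysis set defined elsewhere cannot restore a 4-week VAS that was never taken, and the first criterion is expressly tied to the analysis.

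Three stronger readings are tempting, and the documents do not support them.

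- **That the rule does bias the result, in a known direction.** Bias needs withdrawal to differ between arms in rate or in its link to outcome. The documents do not settle either, so the supported statement is that the comparison can be biased. The 17% is an upper-end illustration.
- **That incomplete records must remove more of group A,** because it has 20 naprapathy sessions on top of 20 physical therapy sessions. The article does not say that each session has its own record. Both therapies run Monday to Friday, so one daily record is equally possible. The criterion also covers only gaps that matter to the final analysis. Any calculation would rest on per-session rates with no source.
- **That the rule hides harm.** The third criterion covers severe reactions and emergent symptoms, with examples such as "aggravation of disease or severe depression and the need for special treatment". Naprapathy-related events go on case report forms, adverse events are reported to the ethics committee, and the Statistical Analysis section summarizes them as counts and percentages. Nothing says that a withdrawn participant's events go uncounted.

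**Conclusion.** The point holds in this form: a stated rule withdraws randomized participants for post-randomization reasons that can relate to arm and outcome, and the single post-baseline assessment means early withdrawal loses the primary outcome. The primary comparison can therefore be biased.

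The size and direction cannot be derived from the documents. Under assumed complete dependence on outcome in one arm, with the article's 10% rate, the shift is about 0.2 SD and type I error about 17%. Under moderate dependence, type I error is about 6% to 8%. The conclusion rests on reading withdrawal as ending assessment, which the article's text suggests but does not spell out. If withdrawn participants are in fact assessed at 4 weeks and analysed as randomized, the problem is one of wording and the article should say so.

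**What to change.** - Delete incomplete treatment records as a reason for withdrawal.
- Separate stopping study treatment from leaving the study. Leave the clinical stopping rule as it is, but reconcile two passages: the withdrawal criteria make withdrawal automatic for severe reactions, whereas the Naprapathy section has treatment suspended after any adverse event and leaves its termination to the investigator. Which of these governs is a clinical matter for the trial team.
- Collect the 4-week VAS, Brunnstrom score and EMG from all randomized participants, whether or not they stopped treatment. For those already withdrawn, recover 4-week data where they exist. The article reports 100 of 116 enrolled by January 2023, so part of this will be retrospective.
- Make the analysis of all participants in their assigned arm primary, with a sensitivity analysis for missing 4-week VAS. Use the present criteria only to define a supportive per-protocol set.

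The cost is a change of protocol wording, one assessment for each participant who stopped treatment, and a little more analysis. The estimated effect may be slightly smaller.

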### Randomization

In this clinical trial, a total of 116 participants with BPI will be randomly assigned to either group A (naprapathy plus physical therapy) or group B (physical therapy) at a 1:1 ratio. The random sequence will be generated using SAS software (version 9.3; SAS Institute, Inc). The coauthors randomizing the participants are not linked to any statistical work.

### Interventions

The treatment plan of this trial is based on naprapathy in clinical rehabilitation for the treatment of BPI. Participants in group A will receive naprapathy in addition to physical therapy, while participants in group B will receive physical therapy only. Treatment in both groups will last 4 weeks. The interventions in this trial involve rigorous naprapathy and physical therapy schedules. To ensure the compliance of naprapathy practitioners and physical therapists with their schedules, they will be asked to undergo pretrial training, after which they will be required to pass an entrance examination to participate in this trial. All included naprapathy practitioners and physical therapists will have at least 5 years of practical experience in clinical rehabilitation.

### Physical Therapy

All participants will receive physical therapy, such as neuromyoelectric stimulation by a transcutaneous electrical nerve stimulator (TENS 21, Homer Ion), medium-frequency electrotherapy by a medium-frequency electrical stimulator (ES-521, Ito), and continuous passive motion by an upper limb continuous passive motion joint rehabilitation device (2029, DJO), once each day for 5 continuous days in a week. Each therapy session will last for 40 minutes and will be performed 5 times a week (from Monday to Friday) for a total of 20 sessions in 4 weeks.

### Naprapathy

For patients with total BPI, the patient will take a sitting position. The naprapathy practitioner will stand on the affected side and first apply Yizhichan (one-finger Zen) (Figure 2) pushing manipulation and press-kneading manipulation at Fengchi (GB 20, affected side), cervical Jiaji points (EX-B2, affected side), Jianjing (GB 21, affected side), Jianyu (LI 15, affected side), Quchi (LI 11, affected side), Waiguan (SJ 5, affected side), and Hegu (LI 4, affected side). Then, the practitioner will apply rolling manipulation (Figure 3) from the affected shoulder to the upper limb and grasping manipulation (Figure 4) on the neck, shoulder, and upper limb. Finally, the hand-shoulder shaking (Figure 5) method will be applied to help soothe the joints. Within the allowable safety range of the affected limbs, the joints of the upper limbs will be passively moved.

For patients with upper trunk BPI, the naprapathy practitioner will apply Yizhichan pushing and press-kneading manipulations at Fengchi (GB 20, affected side), Yunmen (LU 2, affected side), Quchi (LI 11, affected side), Shousanli (LI 10, affected side), Hegu (LI 4, affected side), Yangxi (LI 5, affected side), Sanjian (LI 3, affected side), Yuji (LU 10, affected side), and Laogong (PC 8, affected side). The other methods will be the same as above.

For patients with lower trunk BPI, the naprapathy practitioner will apply Yizhichan pushing and press-kneading manipulations at Tianzong (SI 11, affected side), Jianzhen (SI 9, affected side), Waiguan (SJ 5, affected side), Yangchi (SJ 4, affected side), Jianwaishu (SI 14, affected side), Xiaohai (SI 8, affected side), Yanglao (SI 6, affected side), Yanggu (SI 5, affected side), and Houxi (SI 3, affected side). The other methods will be the same as above.

The duration of each naprapathy session will be 20 minutes and will be performed 5 times a week (every Monday to Friday) for a total of 20 sessions in 4 weeks. If there are any adverse events, the treatment will be suspended, and the investigator will decide whether to terminate the treatment.

All the acupoints used in this study are shown in Figures 6 and 7.

**Figure 2 figure2:**
[figure not shown]
Yizhichan pushing manipulation.

**Figure 3 figure3:**
[figure not shown]
Rolling manipulation.

**Figure 4 figure4:**
[figure not shown]
Grasping manipulation.

**Figure 5 figure5:**
[figure not shown]
Shaking manipulation.

**Figure 6 figure6:**
[figure not shown]
Illustration of acupoints (front).

**Figure 7 figure7:**
[figure not shown]
Illustration of acupoints (back).

